## Abstract

**Background:**

Tourette syndrome (TS) is a developmental neuropsychiatric disorder. Behavior therapy, especially habit reversal training (HRT), has gradually become regarded as one of the core therapies for TS. Mindfulness approaches can improve psychological adjustment and reduce stress and anxiety, suggesting potential benefits when incorporated into behavior therapy. To improve the efficacy of HRT, we combined it with mindfulness, an approach named mindfulness-based habitual reversal training (MHRT). The aim of this protocol is to investigate the efficacy and neural mechanisms of MHRT for TS.

**Methods/design:**

We will perform a randomized control trial (RCT) to evaluate the efficacy and neural mechanisms of MHRT. The sample will include 160 participants (including 120 patients with TS and 40 healthy controls). The patient sample will be randomly divided into three groups exposed to three different types of training: MHRT, HRT, and psychoeducation and supportive therapy (PST). Participants will be assessed and undergo resting-state fMRI scans at baseline and at the end of the 12-week training. The Yale Global Tic Severity Scale (YGTSS) and Premonitory Urge for Tic Scale (PUTS) will be used to assess the severity of tic symptoms and premonitory urges. The primary outcomes are change scores on the YGTSS and other assessments from baseline and the end of the training. The secondary outcomes are the neural correlates of these trainings among these groups based on graph theory, which is used to characterize brain functional connectivity networks. The default mode network (DMN) and the salience network (SN) will be assessed (which have been associated with mindfulness as well as the generation of tic symptoms) by network parameters, including clustering coefficients and shortest path lengths. Changes in these network parameters will be regarded as the neural correlates of the behavioral training.

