#### Sample size estimation

In accordance with the experimental design, three groups of participants will be included: the HRT group, MHRT group, and psychological education and supportive therapy (PST) group.

In addition, for the sample size, we use the formulas (see Supplementary Figure S1) to **calculate** the sample size (α = 0.05, 1–β = 0.8). Taking YGTSS scores as the indicator of a curative effect and based on the effect size of 0.68 calculated in a preliminary pilot test, it was calculated that at least 23 participants were needed in each group, and the drop-out rate was estimated to be 20%. Based on previous experience, 15% of MRI scans have invalid data, resulting in at least 34 subjects being required in each group (38). Therefore, 40 patients will be recruited in each group, for a total of 120 patients in this study. In addition, another 40 healthy controls will be recruited as blank controls for the behavioral and imaging research. A total of 160 participants will be included.

All evaluators will be blinded, and the treatment condition assignment will not be disclosed until after the intervention. The clinical evaluator will not be informed of which therapeutic modality the participants will receive in the evaluation process. Moreover, all dropouts must be accounted for and reported. The reasons for dropouts are mentioned. Intention-to-treat analysis was used to assess the missing data.

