### Assessment procedures

The clinical evaluation process will mainly be completed by two attending child psychiatrists. Before the formal evaluation, an evaluation of the consistency between raters will be completed. The clinical evaluation will be carried out only after the consistency of the raters is above 0.85. The time points for the evaluation mainly included the baseline test, within 1 week after the completion of eight sessions of intervention, and at the end of 1 month after eight sessions of intervention. The patients will be followed up at the end of 3 and 6 months after the eight sessions of intervention. For more details, see Figure 1.

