### Interventions for the different groups

There are three main types of intervention techniques used in this study: traditional HRT, MHRT, and PST. The intervention includes a total of eight sessions, and a consistent time frame will be used with each intervention method. More details can be seen in Figure 2.

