## Limitations

The symptoms of tic disorder are characterized by volatility. Its severity will be affected by life events, emotions, physical diseases such as infection and so on. Such fluctuations will affect our judgment of the treatment effect. To reduce misjudgment, we will use a scale related to life events and emotions in the evaluation and establish a 3-month follow-up period.

To ensure the quality of and effects obtained with this RCT, we will adopt a one-on-one treatment protocol. Due to the lack of therapists, our experiment will take a long time. In this process, participants will be required to come to the clinic at a fixed time every week. This may also result in the loss of these school-age participants. Online training and group therapy may be ways to solve this problem in the future.

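### The primary outcome is left open across up to six clinical scales, with no error control stated for them, and its visit can be read in two ways

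*Protocol article*

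**What the plan says.** **Outcome.** The Methods/design paragraph of the Abstract gives the only definition: "The primary outcomes are change scores on the YGTSS and other assessments from baseline and the end of the training". The same paragraph lists only the neural correlates as secondary. The Assessment instruments section and the Figure 1 legend name six symptom or process scales: YGTSS, PUTS, CY-BOCS, CGI, FFMQ and SCARED. Two other instruments, Kiddie-SADS-L and the Wechsler scale, serve diagnosis and IQ.

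**Where YGTSS leads.** Sample size estimation rests on it alone: "Taking YGTSS scores as the indicator of a curative effect". Statistical analysis sets the clinically meaningful level, a 30% change, on YGTSS alone.

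**Error control.** The last paragraph of Statistical analysis adjusts alpha for between-network connectivity and for subnetwork graph measures. It states nothing for the clinical scales.

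**Timing.** The Abstract says "Participants will be assessed and undergo resting-state fMRI scans at baseline and at the end of the 12-week training". Interventions for the different groups says "The intervention includes a total of eight sessions, and a consistent time frame will be used with each intervention method", and Limitations says "participants will be required to come to the clinic at a fixed time every week". Assessment procedures lists a baseline test and two later evaluations: "within 1 week after the completion of eight sessions of intervention, and at the end of 1 month after eight sessions of intervention". It then adds "The patients will be followed up at the end of 3 and 6 months after the eight sessions of intervention". Limitations instead plans to "establish a 3-month follow-up period".

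**The concern.** A primary outcome has to fix which measure, at which visit, decides whether the trial succeeded. Here the measure is an open set and the visit depends on which sentence is followed. Taken literally, a null YGTSS result alongside a favourable SCARED or FFMQ result, both self-reported, could be presented as success on a primary outcome. The trial was sized for neither scale. The reader could not tell whether the scale or the visit had been settled before the data were seen.

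This is not a detail that an article may leave to an analysis plan. The article does define the primary outcome, and it defines it too loosely.

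**Working it through.** **1. Error control that the plan does state.** For between-network connectivity it gives an alpha of 0.031 for three comparisons with correlation 0.544. The correlation-adjusted Sidak formula is 1 − 0.95^(1/k^(1−r)). With k = 3 and r = 0.544 it gives 0.0306, which rounds to 0.031. Multiplicity is therefore handled explicitly, and reproducibly, for outcomes that the Abstract calls secondary. For the clinical scales there is no figure to reproduce.

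**2. False-positive chance if any one scale counts.** Inputs:
- alpha 0.05 per test (Sample size estimation; two-sided is assumed, as sidedness is not stated);
- one contrast between two arms;
- k scales, with a common correlation between test statistics that is assumed because the document gives none.

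Under independence the chance is 1 − 0.95^k.
- k = 2 (YGTSS and PUTS, the two scales named earlier in the same Abstract paragraph): 1 − 0.95² = 0.0975, about 10%.
- k = 6: 1 − 0.95⁶ = 0.265, about 26%.

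For six correlated scales, 400,000 simulated sets of equally correlated normal statistics were each compared with ±1.96:

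| Assumed correlation | At least one false positive |
|---|---|
| 0.3 | 24% |
| 0.5 | 21% |
| 0.7 | 16% |
| 0.9 | 11% |

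Even at 0.9 the chance is about twice the nominal 5%.

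**3. The visit.** Eight sessions at one per week end near week 8.
- Visit within 1 week after session 8: about week 8 to 9.
- Visit 1 month after session 8: 8 + 4 = 12 weeks, or 8 + 30.4/7 = 12.3 weeks.

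The end of training fits the first visit, and 12 weeks fits the second. If the better of these two visits could be chosen for one scale, the same simulation gives about 9%, 8% and 7% at assumed between-visit correlations of 0.5, 0.7 and 0.9, against a nominal 5%.

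**4. Follow-up.** Assessment procedures has visits at 3 and 6 months after the eight sessions. Limitations has a 3-month period. The two differ, and no text explains why.

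**5. What keeping six primaries would cost.** With a Bonferroni correction each scale is tested at 0.05/6 = 0.0083. At 80% power the required sample size is multiplied by (2.638 + 0.842)²/(1.960 + 0.842)² = 12.11/7.85 = 1.54, whatever the effect size. One primary outcome keeps alpha at 0.05.

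**The case against.** The strongest reply is that YGTSS is plainly the intended lead. It drives the sample size and the 30% threshold, and no passage says that success on any single scale is success of the trial. The six-scale count is an inference from an open phrase, and the Abstract paragraph itself names only YGTSS and PUTS. An error in MHRT's favour is also rarer than an error in either direction: about 12% and 10% at correlations of 0.3 and 0.5 with six scales. All of this stands, so the percentages are conditional and 26% is an upper figure. It does not repair the definition, which places the other scales beside YGTSS without ranking them.

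Four stronger readings are tempting, but the document does not support them.

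- **The primary time matches no scheduled visit.** Two visits fit, and that is the ambiguity.
- **The 3 × 3 analysis contradicts a five-visit schedule.** Assessment procedures lists three evaluation time points and mentions the 3- and 6-month follow-up separately, so three groups by three times is coherent. How the follow-up data are analysed may be left to an analysis plan.
- **The error reaches 50% or 44%** (correlation 0.3 or 0.5) once all three pairwise arm contrasts are counted. This assumes pairwise tests without a preceding overall test. Statistical analysis specifies a mixed ANOVA and does not state such ungated testing. If pairwise tests follow only a significant overall test, the figures return to 24% and 21%. The document does not state that gate either.
- **PUTS has conflicting directions of benefit.** No passage says which direction of the score counts as better, so no contradiction can be shown.

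**Conclusion.** The point holds in this form. The primary outcome is an open set of up to six clinical scales with no hierarchy and no stated error control, and two scheduled visits fit its timing. If any one scale could carry the claim, the false-positive chance for one two-sided contrast would be about 10% with two independent scales and at most about 26% with six. For correlated scales 11% to 24% is more realistic. These figures rest on an any-one-scale rule, which the text permits but does not state, and on assumed correlations. The mismatches on training length and on follow-up length stand without any assumption about success rules; placing 12 weeks at the 1-month visit assumes one session per week.

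**What to change.** Replace the Abstract's definition with a single primary outcome: change from baseline in the YGTSS total (motor + phonic) tic severity score, which the YGTSS section already singles out, at one named visit from Assessment procedures. The visit within 1 week after the eight sessions is the one that matches the end of training. List PUTS, CY-BOCS, CGI, FFMQ and SCARED as secondary.

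Reconcile the 12-week description in the Abstract with the eight sessions and weekly attendance described in the body. Reconcile the 3- and 6-month follow-up in Assessment procedures with the 3-month period in Limitations.

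The change is one of wording. It needs no extra patients and leaves alpha at 0.05. The price is that fewer outcomes can be claimed as primary.

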**Discussion:**

MHRT was newly developed for the treatment of TS. MHRT may lead to greater reductions in tic severity than traditional HRT. Changes in the network parameters of the DMN and SN may show associations with the efficacy of MHRT.

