#### Construction of the network

The template of the neuroimaging research laboratory of Stanford University (Functional Imaging in Neuropsychiatric Disorders Lab website; http://findlab.stanford.edu/functional_ROIs.html) will be used to explore the DMN and SN (54). For the ROIs of the DMN and SN, see Supplementary Tables S1, S2.

We will use the Brain Connectivity Toolbox to extract the connection information between various brain regions and draw the connection diagram at the macro level. This will be used to quantitatively describe the structure, function, connection model and topological characteristics of the human brain network. We will mainly focus on the brain regions related to PUs: the insula, ACC, supplementary motor area (SMA) and prefrontal cortex. We will take the DMN and SN as the main brain function networks to consider.

Degree, global efficiency, local efficiency, path lengths and cluster coefficients will be used to investigate the relationships between the changes in these two brain functional networks and the improvements in tics and PUs and to clarify the possible brain mechanisms underlying the effects of MHRT from the perspective of brain functional networks. We will assess global network integration, segregation and connectivity between modules using the following measures for the DMN and SN: (1) degree: number of edges connected to a node; (2) global efficiency: global transmission capacity of the network; (3) cluster coefficient: degree of network collectivization; (4) local efficiency: nodal connections to within-network nodes; (5) path length: optimal path from one node to another. To assess the reliability of the results and enhance comparability with previous research, exploratory analyses on the absolute Fisher r-to-z transformed Pearson correlation connectivity matrices will be performed using the same graph indices. The calculation formulas for these parameters are presented in Supplementary Figure S2.

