### Statistical analysis

Measures will be analyzed using IBM SPSS Statistics version 22 (IBM, Armonk, NY, United States).

First, the efficacy of MHRT will be tested using repeated measures analysis of variance (ANOVA). A 3 × 3 mixed design will be used to examine the main effects of group (MHRT, HRT or PST) as a between-subjects factor and time point as a within-subjects factor, as well as interaction effects. Second, for the imaging study, we will assess connectivity between the DMN and SN and compute the average Fisher r-to-z transformed Pearson correlations of the resting-state fMRI time-series between the nodes that belong to these resting-state networks. Pearson correlations will be used to replicate earlier functional connectivity studies. For analysis of the abovementioned neuroimaging indices, we will use univariate mixed-model analyses to assess the effects of MHRT and HRT. We will use the after-training outcomes as dependent variables, the group (MHRT, HRT, PST, and HC) as the independent variable and the baseline measure of the outcome as a covariate. We will also perform these analyses correcting for age, years of education and sex.

Measurement data will be presented as the mean ± standard deviation (x ± s). The demographic and efficacy indices of the three intervention groups before and after the intervention will be compared by multifactor analysis of variance (measurement data), and repeated measures analysis of variance and paired *t*-tests will be used for comparisons between multiple groups and before and after the intervention. In addition, we regarded at least 30% changes in YGTSS scores $\left[(\frac{\mathrm{Pr}e_{\left(YGTSS\right)}-Post_{\left(YGTSS\right)}}{\mathrm{Pr}e_{\left(YGTSS\right)}}\right)\times 100\%]$ as the clinically meaningful level.

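### The plan's criterion for a neural correlate of training requires no difference between randomised arms, and its imaging model mixes in healthy controls, names no deciding contrast and has no tic or urge term.

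*Protocol article*

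**What the plan says.** The Abstract (Methods/design) defines the imaging outcome: "The secondary outcomes are the neural correlates of these trainings among these groups based on graph theory". It gives the scan times: "Participants will be assessed and undergo resting-state fMRI scans at baseline and at the end of the 12-week training". It then says how a change will be read: "Changes in these network parameters will be regarded as the neural correlates of the behavioral training". That sentence names no comparator and no link to symptoms.

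Construction of the network states a further aim. Degree, global and local efficiency, path length and clustering coefficient "will be used to investigate the relationships between the changes in these two brain functional networks and the improvements in tics and PUs". The Abstract (Discussion) is more guarded: "Changes in the network parameters of the DMN and SN may show associations with the efficacy of MHRT".

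Statistical analysis gives the imaging model: "we will use univariate mixed-model analyses to assess the effects of MHRT and HRT", and "We will use the after-training outcomes as dependent variables, the group (MHRT, HRT, PST, and HC) as the independent variable". The baseline value of the index is a covariate, and the analysis is also run adjusted for age, years of education and sex. The Pearson correlations in that section are between node time series.

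Limitations accepts that "The symptoms of tic disorder are characterized by volatility" and that this affects judgment of the treatment effect.

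**The concern.** Three things do not fit together.

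- **The interpretive sentence.** Read literally, it lets a pre-to-post change inside the MHRT arm count as a correlate of training. Such a change can also come from tic fluctuation, from development in children aged 7 to 12, or from familiarity with the scanner.
- **The group factor.** Healthy controls are not randomised and do not have tics. An overall test across four groups can be significant because patients as a whole differ from healthy children, with no difference among the three trainings. The text does not say which contrast decides.
- **The missing link.** The plan wants to know whether network change goes with improvement in tics and urges. A model of the post-training index on group and baseline contains neither, so it cannot answer that.

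At stake is the neural-mechanism half of the trial's stated aim. A training effect on the brain, or its relevance to tic benefit, could be claimed on evidence that supports neither.

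**Working it through.** The plan gives no figure on this point, so there is none to reproduce. The check asks which stated or permitted comparisons are exposed to non-specific change, and whether the missing association analysis is practicable.

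**Usable sample.** Sample size estimation gives 40 per patient group, 20% dropout and 15% invalid scans.
- 40 × 0.80 × 0.85 = 27.2, so about 27 per arm and 3 × 27 = 81 patients pooled.
- The same losses are assumed for the 40 healthy controls.

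**Assumptions for the error rates (not in the documents).** There is no true training effect. The network index has a non-specific shift δ of 0.2 to 0.5 SD between scans and a pre-post correlation ρ of 0.4 to 0.6. Tests are two-sided at 0.05.

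**Route 1: change within the MHRT arm, paired test.**
- Noncentrality = δ√27 / √(2(1 − ρ)).
- δ = 0.2, ρ = 0.4: 0.2 × 5.196 / 1.095 = 0.95, rejection about 15%.
- δ = 0.5, ρ = 0.6: 0.5 × 5.196 / 0.894 = 2.90, rejection about 80%.

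**Route 2: overall test of the four-level group factor, baseline-adjusted, with only the patients shifting.**
- With three group means at δ and one at 0, the sum of squared deviations is 3(δ/4)² + (3δ/4)² = 0.75δ².
- Noncentrality λ = 27 × 0.75δ² / (1 − ρ²), with 3 and 4 × 27 − 5 = 103 degrees of freedom.
- δ = 0.2, ρ = 0.4: λ = 20.25 × 0.04 / 0.84 = 0.96, rejection about 11%.
- δ = 0.5, ρ = 0.6: λ = 20.25 × 0.25 / 0.64 = 7.91, rejection about 63%.
- If healthy controls shift equally, simulation (3,000 replicates) keeps this test at about 4% to 5%.

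**Comparison that is protected: the three randomised arms only, baseline-adjusted.** A common shift has no effect on the contrasts. Simulated rejection is about 4.5% to 6%, in line with the nominal 5%.

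**Feasibility of the missing association analysis.** By Fisher z, the detectable value at 80% power is z = (1.96 + 0.84)/√(n − 3), and r = tanh(z).
- Pooled, n = 81: 2.80/√78 = 0.317, r about 0.31. Allowing for four covariate terms (two for arm, two baselines), 2.80/√74 = 0.326, still r about 0.31.
- One arm, n = 27: 2.80/√24 = 0.572, r about 0.52.
- If r were 0.3, power is about 78% pooled and 33% in one arm.
- If the 15% loss applied to each of two scans (the plan applies it once), 40 × 0.80 × 0.85² = 23.1 per arm, 69 pooled, and 2.80/√66 = 0.345, r about 0.33.
- These are for one test. Five indices in two networks make 10. Bonferroni at 0.05/10 = 0.005 would give (2.81 + 0.84)/√78 = 0.413, r about 0.39.

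**The case against.** The strongest reply is that Statistical analysis, not an Abstract sentence, is the operative text. Its model is baseline-adjusted and includes the randomised PST arm. A reader might infer from the Abstract that fluctuation, maturation or rescanning will be reported as the mechanism of MHRT even if PST shows the same change. The documents do not support that: change shared by the randomised arms cancels in MHRT or HRT versus PST. Nor does the plan state a within-arm test for imaging; its paired t-tests are attached to demographic and efficacy indices. The Abstract also speaks of outcomes among the groups. All of this stands and confines the problem to the two routes above.

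A second reply is that a correlate of training is not a correlate of tic improvement, so a randomised difference in a network index earns the label by itself. This also stands. Requiring an association with YGTSS before using the label would withhold it from a genuine training effect on the network.

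A third reply is that an article may leave the association model to a fuller document. A reader might infer that the plan has no intention of linking brain and tics. It does: Construction of the network states that aim. But the article prints the imaging model's terms, its covariates and corrected alpha levels to three decimals, and none of this serves that aim. What it does state, an unconditional reading of change and healthy controls inside the group factor, is not a matter of condensation.

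**Conclusion.** The point holds in a limited form. The Abstract's criterion omits the randomised comparison. The stated imaging model names no deciding contrast and includes a non-randomised group in its group factor. The aim of relating network change to tic and urge improvement has no matching term in that model.

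The exposure is conditional. It is about 15% to 80% false positives if within-arm change is read as the correlate, and about 11% to 63% if the four-group test decides and only patients shift. It is near 5% if the three randomised arms are compared. The first two ranges rest on the assumed shift, correlation and 27 usable per group. They show that the choice of comparison matters and do not predict this trial's error rate. Separately, even a sound randomised difference shows only that allocation affected the network. It does not show that the network change accompanies tic benefit.

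This should be corrected before analysis. It concerns a secondary outcome and does not affect the YGTSS comparison.

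**What to change.** 1. Reword the Abstract sentence and Statistical analysis so that a neural correlate of training means a baseline-adjusted difference between randomised arms: MHRT versus HRT, and MHRT or HRT versus PST. State which contrasts decide. Keep healthy controls out of that test and use their two scans only to describe maturation and rescanning.
2. For the aim in Construction of the network, add a model pooled over the three patient arms: YGTSS change, and separately PUTS change, on network change, with arm, baseline score and baseline network index as terms.
3. Report item 2 as exploratory association, not mechanism or mediation, because scan change and symptom change cover the same interval. With arm in the model, natural tic fluctuation that moves both could also produce an association. Do not make item 2 a condition for item 1.

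The cost is analysis and wording only; the scans and scales are already planned. The downside is that fewer network changes will qualify as correlates, and the association analysis has limited power across several indices.
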